
**Table 1 Tab1:** Primary and secondary outcome parameters

Outcome parameters	Assessments
Primary outcome parameter	Oswestry Disability Index (ODI) at 2-year follow up to measure degenerative lumbar spondylolisthesis-related disability [8]
Secondary outcome parameter	Questionnaire - Timed “Up and Go” test (TUG) [12] - Beck depression inventory (BDI) [10] - Changes in physical and mental health captured by the Short Form (SF)-12v2 [9] - Core outcome measure index (COMI) [30, 31], patient-orientated outcome questionnaire including - visual analog scale (VAS) for back and leg pain - patient’s satisfaction - work disability - social disability - Pain relief on 100-mm VAS for back pain and leg pain - PainDetect Questionnaire (PD-Q) [11] - EuroQoL 5-Dimension (EQ-5D) [9]
	Intraoperative - loss of blood (LOB) - amount of blood transfusion - operative time - length of wound incision - type of wound closure
	Various - duration of hospitalization - device-related complications - surgery-related complications - re-operations - adverse events (AE), severe adverse events (SAE)
	Health care contacts
	Pain medication usage
	Hospital costs
	Radiological evaluation - MRI [13–16, 32] - x-ray evaluation (antero-posterior, lateral, flexion and extension, standing for overall sagittal alignment and differences in lordosis) - CT scan (overall fusion rate, rate of radiological and/or symptomatic adjacent segment disease, rate of pedicle and/or cage system implant failures)
	Serum markers (CRP, leukocytes, TNF-α, IL-6)

The primary study endpoint is the difference in Oswestry Disability Index between treatment groups at 2 years after surgery

*MRI* magnetic resonance imaging, *CT* computed tomography, *CRP* C-reactive protein

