**Fig. 1 Fig1:**
[figure not shown]
Visit plan. Patients will be followed for 5 years after the intervention. AE, adverse event; ASA, American Society of Anesthesiologists; CT, computed tomography; d, day; intra-OP, intraoperative; m, month; MR imaging, magnetic resonance imaging; QST, quantitative sensory testing; pre-OP, preoperative; SAE, severe adverse event; V, visit; VAS, visual analogue scale

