### Selection bias

Selection bias should be avoided by the randomization of the allocated intervention. All patients accomplishing the inclusion criteria are considered for participation and pre-screening lists are kept to justify non-included patients. Performance bias should be avoided by a standardized protocol of postoperative care at our department. Both groups receive the same preopeative and postoperative treatment until discharge. Attrition bias should be avoided by the “intention-to-treat” or “per-protocol” analysis, respectively. Every patient included in the trial will be considered in the overall evaluation.

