### Sample size and power calculation

The sample size calculation is based on the primary endpoint of the study, a difference in the ODI 2 years post intervention [8]. The sample size was calculated based on the two-group *t* test (GraphPad StatMate Software, version 2.0). Based on a minimally clinical important change of 10% on the ODI, standard deviation for the ODI of 20%, significance level of *p* ≤ 0.05, and power of 80%, an estimated 64 patients are required in each of the intervention groups, for the primary endpoint. The current sample size of 154 patients allows for a 20% loss to follow up while maintaining > 80% statistical power [23].

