### Statistical analysis

Primary and secondary variables and their change from baseline will be summarized by treatment group. Endpoints will be analyzed as appropriate in dependence on the data distribution at a two-sided 0.05 level of significance. Detailed descriptive statistics will be provided for the data collected and 95% confidence intervals will be calculated for all relevant estimates. Measurements on the course of follow up will be analyzed by analysis of covariance (ANCOVA) or generalized model alternatives for categorical or semi-quantitative data. Additional covariates, such as baseline measurements, will be included in the model as appropriate. MRI parameters and variables to assess functional neurological status will be summarized descriptively. Imputation of missing data has not been planned. The primary analysis will follow as randomized. All values will be expressed as the mean and standard deviation.

Data are analyzed for normality by the Kolmogorov-Smirnov test. The Wilcoxon signed-rank test or the paired *t* test is used to analyze continuous paired data, while McNemar’s test is used for categorical data. The Mann-Whitney U test and unpaired *t* test, are used to perform group comparisons of continuous clinical outcome variables while the chi-square and Fisher’s exact test are used to analyze intergroup differences in categorized outcome variables and demographic characteristics (age, sex ratio, duration of symptoms, etc.), respectively. Statistical analysis will be performed after recruitment, one year postoperatively and after completion of the last visit of the study population at the specified time points. An interim analysis will be performed 6 and 12 months after recruitment and after completion of the last visit of the study population at the specified time points.

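### The tests named for categorized outcomes ignore observation time; taken literally, they would bias the long-term rates of re-operation and late complications

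*Protocol article*

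**What the plan says.** All references are to the protocol article.

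- Table 1, under Study design, lists as secondary outcomes "device-related complications - surgery-related complications - re-operations - adverse events (AE), severe adverse events (SAE"). It gives no time point and no event rate for them.
- The legend of Fig. 1 states: "Patients will be followed for 5 years after the intervention".
- Statistical analysis assigns tests by type of variable. For two-group comparisons of categorical data, "the chi-square and Fisher’s exact test are used to analyze intergroup differences in categorized outcome variables". Testing is "at a two-sided 0.05 level of significance". Follow-up measurements are to be analysed by ANCOVA, or by generalized models if they are categorical or semi-quantitative. No imputation is planned.
- The same section places analyses after recruitment, at one year and after the last visit, with interim analyses 6 and 12 months after recruitment. Study design expects enrollment to take 2 years.
- Selection bias states: "Every patient included in the trial will be considered in the overall evaluation".
- Sample size and power calculation allows for 20% loss to follow-up, for the ODI at 2 years.

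No Kaplan-Meier, cumulative incidence, log-rank, Cox or person-time method appears anywhere in the article.

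**The concern.** The Background makes safety half of the objective, and the Discussion stresses that long-term results are lacking. The long-term rates of re-operation and late complications are therefore one of the main things readers will take from this trial.

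These events accrue with time. A chi-square or Fisher table needs one yes/no value per patient and treats all patients as equally observed. They will not be, for two reasons:

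- **Loss to follow-up.** A patient lost at 6 months either enters as 5 years event-free or leaves the denominator. Either choice biases the rate.
- **Staggered analysis times.** If the analyses timed from recruitment mean the close of a 2-year enrollment, patients would have 0 to 2 years of observation at the first analysis, 0.5 to 2.5 years six months later and 1 to 3 years at twelve months, even with no dropout. A crude proportion over such a mix has no defined time horizon.

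At stake are the reported 5-year rates and, if loss differs between arms, the safety comparison.

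**Working it through.** **The plan's own figure.** The article gives no figure for re-operations or complications, so only the ODI sample size can be reproduced. With a difference of 10, SD 20, two-sided 0.05 and 80% power, the t test needs 63.8, so 64 per arm, as stated. Then 64 × 1.2 = 76.8, so 77 per arm and 154 in total. The 20% therefore enters only as the allowance for the 2-year ODI.

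**Assumed inputs.** True 5-year risk p from 5% to 30%; loss L by 5 years of 20%, with 30% and 40% as alternatives; constant hazards; loss unrelated to risk.

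**Formulas.** Let h = −ln(1−p) and c = −ln(1−L).

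- Lost patients counted as event-free: A = h/(h+c) × [1 − exp(−(h+c))]
- Event-free lost patients dropped: B = A / [A + exp(−(h+c))]

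For p = 0.15 and L = 0.20: h = 0.1625, c = 0.2231, exp(−(h+c)) = 0.85 × 0.80 = 0.68. A = 0.1625/0.3857 × 0.32 = 0.135. B = 0.135/(0.135 + 0.68) = 0.165.

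| True 5-year risk | A, 20% loss | B, 20% loss |
|---|---|---|
| 5% | 4.5% (−10%) | 5.6% (+11%) |
| 10% | 9.0% (−10%) | 11.1% (+11%) |
| 15% | 13.5% (−10%) | 16.5% (+10%) |
| 20% | 18.0% (−10%) | 22.0% (+10%) |
| 30% | 27.1% (−10%) | 32.6% (+9%) |

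Relative errors are in brackets.

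**Sensitivity.**

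- 30% loss: A about −15% to −16%, B +14% to +19%.
- 40% loss: A about −21%, B +21% to +29%.
- 20% lost by year 2, continuing at that rate: 1 − 0.8^2.5 = 43% lost by year 5. A true 15% then appears as 11.6% under A.
- Half of the risk perioperative, 20% loss: a true 10% appears as 9.5% and a true 20% as 19.0% under A, about −5%.

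**Between-arm test.** Simulation with 77 per arm, 3,000 runs, lost patients counted as event-free. The Monte Carlo standard error near 5% is √(0.05 × 0.95/3000) = 0.4 points.

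| True risks | 5-year loss | Chi-square | Fisher | Log-rank |
|---|---|---|---|---|
| 10% vs 10% | 20% vs 20% | 5.2% | 2.5% | 4.7% |
| 20% vs 20% | 20% vs 20% | 5.3% | 3.1% | 5.1% |
| 20% vs 20% | 10% vs 30% | 6.2% | 3.3% | 4.4% |
| 20% vs 20% | 10% vs 50% | 10.7% | 7.4% | 5.6% |
| 5% vs 20% | 20% vs 20% | 78% | 71% | 78% |

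The first four rows are type I error and the last is power. With equal loss, chi-square and log-rank perform alike. With 10% versus 30% loss and an equal true risk of 20%, the expected crude rates are 19.0% and 16.9%, a spurious difference of 2.1 points.

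**The case against.** The strongest reply is that this is a condensed article and that estimators, censoring rules and reporting times belong in a statistical analysis plan. The chi-square sentence is generic and also covers demographic characteristics. It does not name re-operations or complications, and the section leaves the choice of method open to the data distribution and allows generalized models for categorical follow-up data.

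Much of this stands. That these tests will be used for re-operations is an inference from a general sentence, though a natural one: re-operation yes/no is a categorized outcome, and the generalized-model sentence concerns repeated measurements with baseline covariates. The reply does not dispose of the point, because the article goes beyond silence. It lists its tests in detail, none uses observation time, and the follow-up and analysis times it sets can make observation unequal.

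Stronger readings that a reader might infer are not supported:

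- **That lost patients will be counted as event-free, so harms are understated.** The article does not say how they are handled. Considering every included patient does not settle it, and the two handlings err in opposite directions.
- **That 20% loss is assumed over 5 years.** It is the 2-year ODI allowance. A missed questionnaire also need not mean that a re-operation goes unrecorded.
- **That a false safety difference of about 3 points is to be expected.** Loss of 10% versus 30% by year 2, continued at those rates, does give 13.2% versus 10.0% for an equal true risk of 15%. But it implies 1 − 0.9^2.5 = 23% versus 1 − 0.7^2.5 = 59% lost by year 5. Patients are blinded and share one site, and nothing in the article suggests such a gap.
- **That implant failure is equally affected.** Table 1 places it under CT, and the only routine CT described is at one year, which is a fixed window.

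**Conclusion.** The point holds in limited form. For re-operations and late device- or surgery-related complications, the only two-group tests named for categorized outcomes ignore observation time. Used literally, they would give long-term rates that are biased by loss and, at the staggered analyses, tied to no defined time horizon.

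With a constant hazard and 20% loss spread over 5 years, the error is about 10% relative in either direction: 0.5 to 2.9 points too low, or 0.6 to 2.6 points too high, for true risks of 5% to 30%. It is about half that if half of the risk is perioperative, and roughly two to three times as large at 40% loss. Event rates, loss timing and 5-year loss are all assumptions, since the article gives none.

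The damage is mainly to the reported rates. The between-arm test is nearly unaffected when loss is equal and is biased when loss differs. To conclude that the harm rates are wrong would go too far. For secondary outcomes this is a moderate point, worth correcting because the correction is cheap.

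**What to change.** In Statistical analysis, add a paragraph stating that:

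- re-operation and post-discharge device- and surgery-related complications are analysed as time to first event from surgery, censored at last contact;
- cumulative incidence is reported per arm at fixed times, for example 1, 2 and 5 years, with death as a competing event (Aalen-Johansen, which reduces to Kaplan-Meier if nobody dies), since patients up to age 85 are eligible;
- the difference between arms is given with a 95% confidence interval and a log-rank or Gray test;
- chi-square and Fisher's exact test are kept for intraoperative and in-hospital events, where observation is essentially complete.

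This needs no extra patients or visits. The costs are somewhat wider intervals for the 5-year rates, and event and last-contact dates must be available in the case report form. The article does not say that they are, so this should be checked. These estimates still assume that loss is unrelated to risk, so loss should also be reported by arm.

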## Discussion

The high prevalence of spinal disease, especially the increasing number of patients with degenerative disc disease, extensively increases the demand for spinal fusion surgery [26]. The standard surgical technique used is pedicle screw fixation with transforaminal lumbar interbody fusion [1]. Although it is an established technique, it is nevertheless an invasive intervention with high complication rates that appear to increase with age, blood loss, operative time, and the number of levels treated [2]. Therefore, minimally invasive techniques have been developed to minimize tissue damage, reduce blood loss, decrease narcotic requirement, and shorten the length of hospital stay [27]. The mPACT technique was established as one of these techniques. A posterior lumbar interbody fusion (PLIF) is then additionally used to perform an intervertebral fusion [6]. However, the PLIF is associated with higher rates of nerve tissue damage and extends the duration of operative procedure in comparison with TLIF [28]. In our prospective, clinical, randomized, controlled trial we will thus use TLIF only.

Implant loosening, especially in patients with poor bone nutrition, is another mentionable drawback that may be associated with spinal instrumentation [29]. The mPACT technique offers greater cortical bone contact [3] and therefore shows several promising advantages in biomechanical testing in comparison to traditional pedicle screw fixation. The cortical bone trajectory increases the pullout strength and improves the rigidity of spinal instrumentation [4].

Most clinical data on this subject are based on retrospective investigations or small prospective cohort studies without long-term results [3, 6, 7]. At this time, there are no prospective, clinical, randomized, controlled trials available. With current standards, well-validated outcome instruments are mandatory to provide efficient surgical treatment recommendations for patients with lumbar degenerative disc disease. This trial will contribute to the understanding of the short-term and long-term clinical and radiological postoperative course in patients with lumbar degenerative disc disease in which the mPACT technique is used.

### Trial status

The trial will start in January 2017 at the Department of Neurosurgery, Medical University of Innsbruck.

## Abbreviations

AE: Adverse event
BDI: Beck Depression Inventory
BMI: Body mass index
CRP: C-reactive protein
CT: Computed tomography
EQ-5D: EuroQoL-5 Dimension
IL: Interleukin
MIS: Minimally invasive surgery
mPACT: Medialised posterior screw placement with cortical trajectory
MRI: Magnetic resonance imaging
ODI: Oswestry Disability Index
PD-Q: painDETECT questionnaire
PEEK: Poly-ether-ether-ketone
PLIF: Posterior lumbar interbody fusion
QST: Quantitative sensory testing
SAE: Severe adverse event
TLIF: Transforaminal lumbar interbody fusion
TNF: Tumor necrosis factor
TUG: Timed up and go test
VAS: Visual analog scale
